#### Secondary outcomes

##### Blinded ADHD assessment

The blinded ADHD assessment includes a standardized observation that is carried out using the Disruptive Behavior Diagnostic Observation Schedule (DB-DOS) [34], a method for observational assessment of disruptive behavior. This observation schedule is extended for the TRACE study, in order to also observe and assess ADHD symptoms. Though the Dutch version of the DB-DOS has been developed and validated for children below age 6, it can be extended for use in children aged 6–12 year [34]. We included this promising standardized and blinded observation as secondary outcome (instead of using this blinded measure as primary outcome), because the psychometric properties of the extended version used in the present study are not known yet.

The DB-DOS is divided into three interactional contexts: two examiner contexts and one parent context. In the first examiner context, the examiner is ostensibly responsive to child behavior, the so-called Examiner Engaged context. Second, within the context of minimal support, the child is observed while working independently, with the examiner being busy doing his or her own work (Examiner Busy context). In addition, the examiner also briefly leaves the room to probe potential covert rule-breaking behaviors. The primary caregiver is involved in the Parent context. Procedures are explained to the parent before starting the tasks and parents are provided with simple worded instructions on flip cards. The different tasks, lasting approximately 4 minutes, are parallel across the modules, including frustration, internalization of rules, compliance, and social play tasks. DB-DOS codes are ratings of child behavior ranging from 0 to 3 and comprising two categories: typical (code 0 = normative behavior and 1 = normative misbehavior) and clinically concerning behavior (code 2 = of concern and 3 = atypical). Each item is rated separately for each context by a blinded clinician (blinded to treatment group and time point).

##### Parent & teacher behavioral comorbidity ratings

To assess the presence of emotional symptoms, conduct problems, peer relationship problems and social behavior, parents and teachers are asked to complete the SDQ (25 items), Children’s Social Behavior Questionnaire (CSBQ; 40 items) and Behavior Rating Inventory of Executive Function (BRIEF; 75 items). The SDQ is a time efficient instrument and the most widely used scale in research and clinical practice, to get a reliable and valid assessment of internalizing and externalizing problems and the impact thereof on family and school functioning in children aged 3–16 years old [30]. The Dutch version of the CSBQ is a well validated, reliable instrument to assess milder forms of autism spectrum symptoms [35]. Items are answered on a 3-point scale ranging from 1 (*not applicable*) to 3 (*clearly applicable*) with higher scores reflecting more autism symptoms. The Dutch version of the BRIEF is a well validated, reliable instrument to assess executive functioning problems [36]. Items are answered on a 3-point scale ranging from 1 (*never*) to 3 (*often*) with higher scores reflecting more executive functioning problems. To assess five distinct features of impulsive behavior, parents fill out the Urgency, Premeditation, Perseverance, Sensation seeking, and Positive urgency Impulsivity scale (UPPS-P) [37, 38]. Each item of the UPPS-P is rated on a 4-point Likert scale ranging from 1 (*strongly agree*) to 4 (*strongly disagree*). Finally, parents fill out the Emotion Dysregulation Inventory (EDI) which is a caregiver-report questionnaire assessing emotion dysregulation symptoms. The EDI consists of 32 items which are rated on a 5-point scale (*not at all* to *very severe*) regarding the emotion dysregulation symptoms occurring in the previous 7 days. In addition, the items are also scored on a ‘lifetime’ prevalence scale, ranging from ‘same, worse, better, or new (symptom never occurred before)’. The psychometric properties of the Dutch versions of the UPPS-P and EDI are not known yet.

##### Cognitive performance

Cognitive assessment is performed using the Cognitive Task Application (COTAPP) [39]. This Dutch computerized neurocognitive assessment tool is designed to measure (variability in) processing speed, attentional and executive control, working memory and learning speed. The COTAPP is a two-choice reaction time paradigm and consists of seven blocks, in which the child is guided through the different paradigms in a play-like manner. By default no coaching is offered to the child. If the child does not succeed in completing the task without the assistance of the examiner, coaching or help can be offered in a structured manner. The amount of offered help is coded by the examiner and included in the outcome parameters. Furthermore, the level of verbal and motor activity of the child during performance can be coded. Validity and reliability of the COTAPP have been confirmed [39], with COTAPP relating significantly to intelligence, school performance, ADHD and Autism Spectrum Disorder symptoms and quality of the student-teacher relationship.

##### School performance

School performance is evaluated on the basis of the monitoring system used in Dutch schools. This monitoring system includes a set of standardized tests measuring motor development, language development (reading, spelling, reading comprehension) and arithmetic skills. Performance level is expressed in percentiles compared to age-matched norms. With the permission of the parents, data can be easily obtained by contacting the school of the child. A change score per domain will be calculated and used to assess school performance.

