**Secondary outcomes**		
Blinded ADHD assessment	T0, T1, T4	DB-DOS
Parent & teacher comorbidity ratings	T0, T1, T4	SDQ, CSBQ, BRIEF, UPPS-P, EDI
Cognitive performance	T0, T1, T4	COTAPP
School performance	T0, T4	Monitoring system Dutch education
Motor activity and sleep pattern	T0, T1, T4	Actigraph
Physical measurements	T0, T1, T4	Weight, height, blood pressure, heart rate
Somatic complaints	T0, T1, T2, T3, T4	Pittsburgh side-effects rating scale
Sleep problems	T0, T1, T2, T3, T4	5-item questionnaire
Quality of life	T0, T1, T2, T3, T4	EQ-5D
Food consumption & eating habits	T0	Questionnaire dietary pattern
	T0, T4	Nutritional assessment (‘Eetmeter’)
Nutritional quality	T0, T2, T3, T4	Nutritional assessment (‘Eetmeter’)^b^
	T0, T1, T2, T3, T4	Expert view
	T0, T1, T4	Blood sample
Carer-related quality of life	T0, T1, T2, T3, T4	CarerQol, PSQ
Parenting styles and family functioning	T0, T1, T4	FFQ, BSBP
Adherence	T1, T4	Morisky Adherence Scale, food diary, separate questions
Satisfaction	T1, T4	GGZ-Thermometer
Cost measurements	T1, T2, T3, T4	Tic-P

*WPPSS-III* Wechsler Preschool and Primary Scale of Intelligence, *WISC-III* Wechsler Intelligence Scale for Children, *GHQ* General Health Questionnaire, *SWAN* Strengths and Weaknesses of ADHD-symptoms and Normal-behaviors (SWAN) rating scale, *SDQ* Strength and Difficulties Questionnaire, *DB-DOS* Disruptive Behavior Diagnostic Observation Schedule, *CSBQ* Children’s Social Behavior Questionnaire, *BRIEF* Behavior Rating Inventory of Executive Function, *UPPS-P* Urgency, Premeditation, Perseverance, Sensation seeking, and Positive urgency Impulsivity scale, *EDI* Emotion Dysregulation Inventory, *COTAPP* Cognitive Task Application, *PSQ* Parenting Stress Questionnaire, *EQ-5D* EuroQol Five Dimensions Health Questionnaire, *FFQ* Family Functioning Questionnaire, *BSBP* Brief Scale of Parental Behavior, *Tic-P* Trimbos and iMTA questionnaire on Costs associated with Psychiatric illness’

^a^T0 baseline; T1 five weeks after baseline; T2 four months after baseline; T3 eight months after baseline; T4 12 months after baseline. ^b^ Only parents of healthy diet participants who continue the diet after five weeks, register food consumption at T2 and T3

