### Sample size and power

The justification of sample size is calculated based on the assumption of superiority: we assume that the ED is more effective than the healthy diet on the ordinal primary outcome respondership (i.e. five categories: full responder, partial responder, mixed responder, non-responder and deterioration). A clinically relevant outcome is defined as detecting twice as many full responders in the ED group than in the healthy diet group. Each dietary group includes 81 children. With this sample size and using ordinal regression, the power is 0.99 (α = 0.05, two sided test) to detect double the amount of full responders in the ED compared with the HD (Table 4: scenario 1). In addition, the power to detect one and a half times as many full responders in the ED compared with the healthy diet is 0.64 (α = 0.05, two sided test) (Table 4: scenario 2).

**Table 4 Tab4:** Hypothetical Distribution of Participants for Power Calculation

	Full responder	Partial responder	Mixed responder	Non-responder	Deterioration
Scenario 1					
Elimination diet	16 (20)	45 (55)	10 (12%)	6 (8%)	4 (5%)
Healthy diet	8 (10%)	24 (30%)	21 (25%)	16 (20%)	12 (15%)
Scenario 2					
Elimination diet	12 (15%)	37 (45%)	13 (16%)	11 (14%)	8 (10%)
Healthy diet	8 (10%)	24 (30%)	21 (25%)	16 (20%)	12 (15%)

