### Statistical analyses

All primary analyses will be Intention To Treat. The primary outcome will be measured as an ordinal variable with five categories. Therefore, the effect of the intervention will be measured in terms of odds ratio, comparing odds for reducing ADHD symptoms and emotion dysregulation symptoms in the elimination diet group with the corresponding odds in the healthy diet group. Multiple logistic regression analyses will performed to compute the odds ratio and 95% confidence intervals, using ordinal logistic regression analysis. The CAU group will be used as a reference group.

Differences in continuous outcome measures between the dietary trajectories will be determined with analyses of ANCOVA. The follow-up value (T1, after five weeks) will be added as the dependent variable and the baseline value will be added as covariate. The two dietary groups will be compared on all outcomes at T1, using T0 scores as covariates. Clinical significance will be estimated using the partial eta squared effect. The CAU group will be used as a reference group.

In addition, a repeated measures ANOVA will be performed. First, the whole sample will be used (Intention to Treat) to determine whether adding a dietary treatment has beneficial outcomes on costs and effects of the whole treatment trajectory after 12 months (regardless of continuing the dietary treatment after 5 weeks or not). Next, per-protocol and post-hoc analyses will be performed using repeated measures ANOVA where the main outcome measures will be compared across the three conditions (i.e. elimination diet; healthy diet; CAU). Also, we will determine how many children adhered to the diet after 12 months, whether the intervention effects maintained after 12 months, which products are eliminated from the diet after 12 months and the nutritional quality of the attained diet after 12 months.

Finally, two moderator analyses will be performed: one comparing dietary responders versus non-responders (predicting respondership) and another comparing children/families adhering to a dietary treatment versus children/families that are not able to do so (predicting adherence). Both moderator analyses will be performed to compare children/families after 5 weeks and after 1 year of treatment.

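### School performance is assessed by a change score, on the plain reading of percentiles, with no T0 adjustment stated at T4: unbiased between the randomised diets, but less precise than it need be

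*Protocol article*

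**What the plan says.** The Protocol article, School performance, describes standardised tests from the monitoring system used in Dutch schools and names one scale for them: "Performance level is expressed in percentiles compared to age-matched norms". It then defines the quantity to be analysed: "A change score per domain will be calculated and used to assess school performance".

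Table 3 lists the outcome at two time points: "School performance T0, T4 Monitoring system Dutch education". There is no T1 measurement.

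Statistical analyses prescribes ANCOVA for continuous outcomes, but at T1: "The follow-up value (T1, after five weeks) will be added as the dependent variable and the baseline value will be added as covariate". The scope is repeated as "The two dietary groups will be compared on all outcomes at T1, using T0 scores as covariates". For the 12-month comparisons the section turns to another model: "In addition, a repeated measures ANOVA will be performed".

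**The concern.** The article's own method for continuous outcomes is to adjust the follow-up value for baseline. School performance falls outside that rule only because the rule is tied to a visit at which the outcome is not collected. What is left for it is a change score with no covariate stated. The repeated measures ANOVA does not fill the gap: with two time points, its group-by-time test is the same test as an unadjusted comparison of change scores.

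Two things are at stake. First, the one-year school comparison would have a larger standard error than the data already collected allow. Second, if the change is taken on percentiles, the mean change gives different weight to the same real improvement depending on where a child starts, with least weight in the tails.

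**Working it through.** The article gives no power or precision figure for school performance. Its only power figures, 0.99 and 0.64, are for the ordinal primary outcome. Simulating the proportional-odds score test on the Table 4 distributions with 81 per arm gives 0.99 for scenario 1 and 0.62 to 0.65 for scenario 2. Those figures are reproduced, and this point does not touch them.

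**Inputs.** From the article: T0 and T4 measurements only; 81 children per diet. Assumed: equal SD at T0 and T4 (set to 1) and a T0–T4 correlation r, which the article does not give. The working range is 0.5 to 0.8, with 0.9 shown as well.

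**Step 1: precision.**

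- Variance of the change score: 2(1 − r)
- Residual variance under ANCOVA: 1 − r²
- Ratio, ANCOVA to change score: (1 − r²) / [2(1 − r)] = (1 + r)/2

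| r | Change score | ANCOVA | Ratio | 81 per arm on change score is worth, under ANCOVA |
|---|---|---|---|---|
| 0.5 | 1.00 | 0.75 | 0.75 | 81 × 0.75 ≈ 61 |
| 0.7 | 0.60 | 0.51 | 0.85 | 81 × 0.85 ≈ 69 |
| 0.8 | 0.40 | 0.36 | 0.90 | 81 × 0.90 ≈ 73 |
| 0.9 | 0.20 | 0.19 | 0.95 | 81 × 0.95 ≈ 77 |

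The ratio is below 1 for every r below 1, so the direction does not depend on the assumption; only the size does. For illustration, with an assumed effect of 0.4 SD and 81 per arm all measured at T4, power is 0.72 (change) against 0.84 (ANCOVA) at r = 0.5, and 0.91 against 0.95 at r = 0.7.

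A simulation on the percentile scale itself gives change-to-ANCOVA variance ratios of 1.35, 1.19 and 1.12 for underlying r of 0.5, 0.7 and 0.8. The formula gives 1.33, 1.18 and 1.11. The loss is therefore present on percentiles too.

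**Step 2: does an unadjusted change score bias the diet comparison?** Given a realised T0 difference d between the diets, the change-score estimate is displaced from the ANCOVA estimate by (1 − r)d in size. Under randomisation d averages zero, so there is no bias. In the same per-child units, the variance that this displacement adds is (1 − r)², and (1 − r²) + (1 − r)² = 2(1 − r). That is exactly the change-score variance of step 1. The displacement and the loss of precision are one effect.

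**Step 3: percentile spacing, assuming normal norms.** The SD distance is the difference of normal quantiles.

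- 50th to 40th percentile: 0.25 SD
- 20th to 10th percentile: 0.44 SD

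Conversely, the same 0.3 SD gain is recorded as +11.8 points from the 50th percentile, +6.3 from the 10th and +3.9 from the 5th.

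**The case against.** **The article does not say that untransformed percentiles are subtracted.** It names the percentile as the scale and, separately, a change score. This stands. Differencing percentiles is the plain reading, because no other scale is named, but it is not explicit. If another score were differenced, step 3 would fall and step 1 would remain.

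**A change score does not rule out a baseline covariate.** Change regressed on arm and T0 gives the same arm effect as T4 regressed on arm and T0. The outcome description names a variable, not a model, and a condensed article may leave the model to a fuller document. This also stands in part: a reader might infer a decision to omit T0, and the text does not show one. What it does show is a baseline-adjusted rule tied to the wrong visit for this outcome, and a 12-month model that is equivalent to unadjusted change.

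**A reader might infer that chance imbalance at T0 biases the elimination diet versus healthy diet difference.** The documents do not support that. The diets are randomised, so the comparison is unbiased, and step 2 shows that quoting a displacement as well as a larger standard error counts one thing twice. A 0.2 SD imbalance would shift the estimate by 0.04 SD (r = 0.8) to 0.10 SD (r = 0.5), but the standard error of a T0 difference with 81 per arm is √(2/81) ≈ 0.16 SD, so 0.2 SD is larger than typical. The care-as-usual arm is not randomised. There T0 levels may differ systematically and regression to the mean could matter, though ANCOVA would not remove all confounding either.

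**Percentiles have a purpose, and normal scores have limits.** Age-normed percentiles take out expected growth over the year and are easy to read. Normal scores do not cure a floor, are undefined at 0 and 100, and magnify rounding in the tails. An underlying ability score is not mentioned in the article, so its availability cannot be assumed. All of this stands, and it is why the scale change is a preference with a condition attached.

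**Conclusion.** The point holds as a minor improvement to one secondary outcome. As written, nothing in the article adjusts the one-year school comparison for T0. Adjusting would cut the variance to 0.75 to 0.90 of that of the change score for r between 0.5 and 0.8, and to about 0.95 at r = 0.9. The size rests on an assumed correlation and equal SDs. The gain is certain in direction and modest if r is high.

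The comparison of the two diets is unbiased either way. The scale point rests on the plain reading that percentiles are differenced and on normal norms. How many children it affects cannot be told, because the article gives no T0 distribution. The primary outcome, its analysis and the sample size are unaffected.

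**What to change.** Extend the article's own ANCOVA to T4 for this outcome: per domain, compare the diets on the T4 school score with the T0 score as covariate. Keeping the change score and adding T0 as covariate gives the same arm effect, so either wording will do.

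State the scale. Preferably analyse normal scores of the percentiles, with a rule fixed in advance for values at or near 0 and 100, and report percentiles descriptively.

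The cost is analysis wording only. T0 and T4 percentiles are already collected, and no new data are needed.

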##### Motor activity and sleep pattern

Motor activity and 24 h sleep/wake measurements including total sleep time (TST), sleep latency and wake after sleep onset (WASO) are objectively and non-invasively measured using actigraph recordings in the home situation (http://www.actigraphcorp.com/products/wactisleep-bt-monitor/), allowing for a participants’ activity information to be obtained in a natural setting for a prolonged and continuous period of time. Participants are asked to wear a wrist actigraph during a full week. The mean and variance of activity ratios of mutually exclusive intervals are analyzed from low-level to high-level (0.5–2.8 G) [40].

##### Physical measurements

Blood pressure, heart rate, height, weight, sleep problems and somatic complaints are routinely monitored at every visit as part of standard clinical care. Sleep problems will be examined using a 5-item questionnaire (answered with ‘yes’ or ‘no’) used in standard clinical care assessing problems with falling asleep, maintaining sleep and total amount of sleep compared to children of the same age. Somatic complaints (e.g. headache, nausea) will be assessed using the frequently used Pittsburgh side-effects rating scale (translated to Dutch) [41]. The 18 items can be answered on a 4-point scale ranging from 0 (*none*) to 3 (*severe*).

##### Quality of life

Health related quality of life (HRQL) is assessed using the EQ-5D Youth [42]. The English version is a validated generic HRQL instrument, that measures quality of life based on 5 dimensions: mobility, self-care, usual activities, pain/discomfort and anxiety/depression. Each dimension is assessed by one question with a 3-point response scale ranging from 0 (*no problems*) to 2 (*severe problems*) of which higher scores indicate greater impairment. In addition, parents are asked to rate the overall health of their child on a scale from 0 to 100. This questionnaire has been used in the Netherlands for assessments of quality of life in children with ADHD [42].

##### Food consumption and eating habits

Food consumption of the child (all treatment conditions) will be measured through an online tool (‘Eetmeter’, Dutch Nutrition Center) available at the website of the Dutch Nutrition Center or as a mobile app (free of charge). This tool has an extensive catalogue of products found in the Dutch supermarkets, including the common quantitates in which they are eaten. Users can enter per main meal (breakfast, lunch and dinner) or between main meals (snacks) the foods that are consumed. Parents are asked to report all food consumed by the child, for two weekdays and one weekend day and send this information to the research staff by email (an export function is part of the online tool). Based on the Dutch Food Composition Database (NEVO) nutrient intake can be calculated from the food consumption data [43]. In addition, parents fill out a general questionnaire (specifically developed for the present study) at baseline assessing the current eating habits, daily meal structure and family eating rules. This includes questions about whether the child has (food) allergies/ intolerances, follows a specific diet or uses dietary supplements, how often per week a child consumes breakfast, lunch and dinner and the number of snacks between the main meals. This questionnaire also assesses whether main meals are consumed on regular times each day, whether children have to follow certain rules (e.g. leaving table when finished, eating at the table) and how often children do not eat at home.

##### Nutritional quality

Nutritional adequacy of the overall diet is continuously monitored and regularly registered by the dietician during the whole study (based on the ‘Eetmeter’ and expert view). For the ED group, this is registered after phase one of the reintroduction phase and at the end of the reintroduction. For the healthy diet group, this is registered after one week, four and eight months of the diet. If necessary, dietary supplements are recommended to the children after T1. Also, a blood sample (15 ml) is drawn from children randomized to the elimination diet or healthy diet. Blood samples are fractionated into serum and subsequently stored at − 80 °C until further use. If nutritional deficits are expected in long term users of ED, it is possible to measure the level of those specific minerals or vitamins.

##### Adherence

Adherence to treatment is measured using the Morisky Adherence Scale [44]. The English version of this scale is the most validated scale for measuring non-adherence in clinical practice and distinguishes between intentional and unintentional non-adherence. The scale has been adapted in order to assess also adherence to a dietary treatment. The scale consists of eight items which parents can rate on a 5-point scale ranging from 0 (*never*) to 5 (*always*). Higher scores reflect more problems adhering to the treatment. During every weekly consult, dieticians register if children deviated from the diet, and what parents experienced as easy and challenging during the last week of the diet. In addition, dieticians and parents assess adherence on a 10-point scale (ranging from 1 *no adherence to the diet* to 10 *perfect adherence to the diet)* every week. Also, parents fill out a food diary during the first week of the diet which helps dieticians to assess adhering to the diet. Compliance to the dietary restrictions, foods that are used to replace the ‘forbidden’ foods and the use of dietary supplements (prescribed or on own initiative) are queried at the end of the study.

